## Authors’ Contributions

All authors contributed to the writing of and critical review of the manuscript from its inception to the final version submitted for publication.

## Abstract

Background: Depersonalisation-Derealisation Disorder (DDD) is a distressing mental health condition which causes individuals to have a sense of ‘unreality’ or detachment about themselves and/or the world around them. DDD is chronically under-researched, and as a result, under-diagnosed, with a population prevalence of about 1%. In systematic reviews, Cognitive Behavioural Therapy (CBT) has been found to be the only intervention with significant clinical impact on alleviating the symptoms of DDD. However, previous studies have suffered from small sample sizes, reliance on expert clinicians to provide therapy and narrow population demographics. This feasibility randomised controlled trial aims to provide more robust evidence for the treatment efficacy of CBT in DDD.

**Methods**: The study aims to recruit 40 participants from two NHS trusts, 20 per arm from two community Mental Health NHS services in London. The intervention group will receive 12-24 individual CBT sessions over a 6-month period from CBT therapists following specialist training for DDD. The control group will receive Treatment as Usual. We will assess the feasibility of a future RCT through measuring the acceptability of the intervention, and assessing our ability to recruit, retain and randomise participants. We will calculate the correlation of scores on the Cambridge Depersonalisation Scale, its baseline standard deviation, assess the magnitude/direction of change and characterise the uncertainty in the outcome scores and the probability that the results have been obtained by chance.

**Discussion**: The outputs of this trial will guide whether a definite RCT is feasible and acceptable, for both the clinician and participant.

Trial Registration: The ISRCTN registration number is ISRCTN97686121(<https://doi.org/10.1186/ISRCTN97686121>).

Keywords: CBT, Derealization, Depersonalization, NHS, Trial, Feasibility

## Background

Depersonalisation Derealisation Disorder (DDD) is a distressing mental health condition where a person has a profound sense of disconnection and unreality about themselves and/or the world (1). Systematic reviews estimate the prevalence of DDD in community surveys at around 1%, which is similar to rates of schizophrenia and obsessive-compulsive disorder (2–4). The prevalence of DDD amongst mental health service users is higher at approximately 20%, usually in combination with other disorders (3,4). However, there is a gap between true prevalence rate and clinical diagnosis; chronic under-diagnosis of DDD, often coming after delays of several years, has contributed to the widely held, but erroneous, assumption that DDD is rare(5). Consequently, there has been underfunding of research into effective treatments. There is currently no National Institute of Care Excellence (NICE) guidance on treatments for DDD (6). Recent lobbying of parliament has achieved formal acknowledgement of the urgent need for more research (7).

Cognitive behavioural therapy (CBT) is the most widespread psychological therapy used in the NHS with effectiveness demonstrated across a wide range of conditions (6). CBT seeks to identify cognitive (i.e., thoughts and thinking processes), emotional and behavioural factors that might perpetuate symptoms and seeks to find more helpful alternatives (8). Although the basic cognitive and behavioural theory of emotion and behaviour remains the same, adaptations of CBT to different disorders consider the most relevant areas to address in therapy (8,9).

In systematic reviews of the existing evidence of treatment for DDD, the strongest evidence is for CBT that has been adapted for the specific condition (CBT-f-DDD), with little benefit demonstrated from a variety of medications and other therapy modalities (10). Wang et al.,’s (9) recent systematic review comprehensively covered both psychiatric and therapeutic modalities for treating DDD concluding that the evidence was poor, heterogenous and cannot support clinical treatment. The main treatment modalities discussed included medication primarily the use of lamotrigine and selective serotonin reuptake inhibitors (SSRIs) (11–13); neuromodulation of the temporo-parietal junction and ventrolateral prefrontal cortex through repetitive transcranial magnetic stimulation (14); and CBT methods as described in this study (15–17).

There have been two uncontrolled studies of consecutive referrals of patients with DDD to a tertiary specialist clinic (15,16). In the first of these, 21 participants, with longstanding severe symptoms which had not responded to medication or previous psychological therapies, were treated with a median of 11 individual adapted CBT-f- DDD sessions (IQR: 7 to 18). There was a statistically significant reduction in state DDD symptom severity (Effect Size = 0.37, 95%; [C.I: 0.12 to 0.53]) with 29% of participants no longer meeting diagnostic criteria at the end of therapy. Additionally, participants experienced a reduction in the severity of general dissociation (Effect Size = 0.34; [95% C.I: 0.10 to 0.51]). A recent analysis of outcomes of 36 participants from the same clinic has replicated these initial findings (15). A mean decrease in trait DDD symptoms (Mean = -33.67; [95% C.I: -45.14 to -22.20]) was observed after a median of 16 sessions of CBT (IQR: 10 to 16), with additional statistically significant reductions in anxiety and depression symptoms during the treatment period relative to the waitlist period.

There are several methodological limitations to these studies: participants were not randomised, participants were only recruited from one tertiary specialist clinic and therefore may not be typical of those in generic primary and secondary care settings, and a small number of clinicians delivered the intervention. It is not possible to make concrete inference about the effectiveness of CBT for DDD or about its generalisability using these limited data.

### Summary and research questions

Given the relative paucity of robust information about the effectiveness of CBT for DDD currently available, and not having the necessary parameters with which to conduct a sample size calculation for a fully powered definitive RCT, we are carrying out a feasibility study to assess the feasibility and acceptability of carrying out a future RCT of CBT for DDD.

## Methods/Design

This project will use a two-arm parallel group (single blinded to assessor) individually randomised design consisting of active CBT treatment versus Treatment As Usual (TAU). Participants will undertake an eligibility assessment (T0) and will be assessed again prior to commencement of treatment (T1). Participants randomised to the treatment condition will receive a minimum of 12 weekly CBT sessions (up to a maximum of 24) during a 6-month intervention window. Once the intervention is complete, all participants will be assessed again (T2, 6 months after the eligibility assessment). The final follow-up assessment will occur for all participants nine months after the eligibility assessment (T3).

### Aims and Objectives

The aims of the study are to:

1. Investigate the ability to recruit, randomise and retain participants through the study period,
2. Define the parameters to inform the sample size calculation for a future efficacy trial (RCT) (i.e., to obtain the correlation coefficient of scores from the Cambridge Depersonalisation Scale (CDS) at baseline and at follow-up) as well as the pooled standard deviation of the CDS at baseline,
3. To carry out preliminary inferential analyses of the efficacy of the therapy to check if a signal has been detected in the treatment arm versus the control arm (so as to inform a subsequent larger RCT if appropriate). These analyses may include estimating the magnitude and direction of the treatment effect as well as obtaining an estimate of the uncertainty in the estimate.
4. To perform a within-trial economic evaluation to compare the costs and outcomes of the intervention group versus the standard care group,
5. Disseminate specialist CBT-f-DDD skills to generic NHS clinicians,
6. Determine whether CBT-f-DDD can be conducted within typical NHS settings with generic CBT therapists given a brief training in DDD.

### Participants

The study will aim to recruit 40 participants, 20 participants in each arm. All participants will be aged between 16-75, living in London, and have symptoms of Depersonalisation and/or Derealisation currently meeting DSM-V (1) criteria for DDD. This will be assessed by the research assistant (RA) in their initial (T0) screening interview by asking the participant the following two questions, which make up part of the diagnostic criteria in the DSM-V (1) :

“Over the last two weeks, how often have you had:

1. Experiences of unreality, detachment, or being an outside observer with respect to one's thoughts, feelings, sensations, body, or actions (e.g., perceptual alterations, distorted sense of time, unreal or absent self, emotional and/or physical numbing). [Depersonalisation]

0 =not at all; 1=several days; 2=more than half the days; 3=nearly every day”

1. Experiences of unreality or detachment with respect to surroundings (e.g., individuals or objects are experienced as unreal, dreamlike, foggy, lifeless, or visually distorted). [Derealisation]

0=not at all; 1=several days; 2=more than half the days; 3=nearly every day.”

The total score will be calculated as follows:

1. Total score = (a + b).
   1. Scores <3 = mild-moderate DDD.
   2. Scores >=3 = moderate-severe DDD.

Other DSM-V criteria will be assessed including intact reality testing, that the symptoms result in significant distress and/or functional impairment, and that the DDD symptoms cannot be better explained by another condition. Participants will be excluded if they have any of the following co-morbid diagnoses: any psychosis spectrum disorder, substance dependence, intellectual disability, Post Traumatic Stress Disorder (PTSD), or cognitive impairment due to head injury or organic disorder. Comorbidity with anxiety and/or depressive disorders will not be an exclusion criterion.

Additionally, participants will be excluded from the study if they have previously received CBT specifically for the treatment of DDD; have a score below clinical severity (i.e. total score < 3) on the diagnostic questions; cannot provide informed consent; do not have sufficient proficiency in English to engage in CBT; require special communication needs arrangements; are not registered with a GP practice or are involved in any other mental or physical research studies (including drug trials).

**Diversity and Inclusion.** To increase the likelihood that the study sources a representative sample, recruitment will take place across two London mental health trusts covering six boroughs. Camden and Islington NHS Foundation Trust (C&I) is an inner London trust which had over 45,600 service users in 2020 (18). The trust covers the boroughs of Camden, Islington, and Kingston. Islington is the most densely populated local authority area in England and Wales and is among the poorest 20% of neighbourhoods in England (19). Barnet, Enfield and Haringey NHS Foundation Trust (BEH) is an outer London trust which had 146,000 service users in 2022 (20). Approximately a third of individuals across all six boroughs are residents from black, Asian or minority ethnic groups (19, 21–25). We will be recruiting from primary, secondary and tertiary care services across these Trusts.

### Sample Size

There is no formal sample size calculation, or priori power calculation. Instead, a minimum of 24 participants, 12 in each arm, has been suggested for pilot studies (26). This minimum recruitment strategy requires recruiting 29 eligible participants in total (encompassing a nominal 20% dropout rate). This study aims to recruit 20 participants in each arm who complete. We believe this number will give us a final sample large (and sufficiently diverse) enough to assess the practicalities of recruitment, retention, randomisation, and intervention delivery, as well as to obtain the necessary data for the statistical inferences required.

A previous naturalistic self-controlled cross-over study found the effect size between the treatment period and the waiting period to be 0.52 (improvement in favour of treatment). This translated into a decrease of 36 points on the CDS Scale. Using this change score, a correlation of 0.9 which was observed for intra-participant correlation, and the standard deviation of the CDS at each phase of the crossover study, we anticipated that the required sample size would be 29 participants per arm (using the ANCOVA method). Our planned recruitment of 20 per arm provides sufficient power to provide information on the magnitude, direction, and precision of the treatment effect from the feasibility study to power (with sufficient precision) a subsequent definitive RCT if appropriate (15).

To meet our relatively conservative aim of 20 participants completing the trial in each arm we will need a recruitment rate of 5-10 participants a month during the 6-month recruitment period. Historical data demonstrates a referral rate of one referral per week, which would be adequate for the proposed sample size.

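### The protocol uses 20 per arm both as the number recruited and as the number completing, with no dropout allowance on the 40

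*Protocol*

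**What the plan says.** Three places give 20 per arm as the number **recruited**:

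- Abstract: "The study aims to recruit 40 participants from two NHS trusts, 20 per arm".
- Participants: "The study will aim to recruit 40 participants, 20 participants in each arm".
- Sample Size, second paragraph: "Our planned recruitment of 20 per arm provides sufficient power" to inform on the magnitude, direction and precision of the effect.

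Two places give it as the number **completing**:

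- Sample Size, first paragraph: "This study aims to recruit 20 participants in each arm who complete".
- Sample Size, third paragraph: "To meet our relatively conservative aim of 20 participants completing the trial in each arm", followed by a required rate of 5 to 10 recruits a month over six months.

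Dropout is quantified once, for the pilot minimum. The section notes that "a minimum of 24 participants, 12 in each arm, has been suggested for pilot studies" and continues: "This minimum recruitment strategy requires recruiting 29 eligible participants in total (encompassing a nominal 20% dropout rate". No such allowance is attached to the 40.

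**The concern.** A recruitment target and a completer target cannot be the same number when dropout is expected. Recruiting, randomising and retaining participants is the first of the listed aims, and the Analyses section lists recruitment and withdrawals among the evidence for feasibility. If 40 are recruited and 32 complete, the trial has met the aim stated in the Abstract and Participants and missed the aim stated twice in Sample Size. Unless the protocol says which applies, the choice can be made after the numbers are known. The same ambiguity affects the statement on precision, because the analysable number depends on which reading is meant.

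**Working it through.** **Inputs, all from Sample Size unless noted.** Target 20 per arm, 40 in total (also Abstract and Participants); nominal dropout d = 0.20; pilot minimum 24; inflated minimum 29; recruitment 5 to 10 a month for 6 months.

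**Reproducing the plan's own figure.** The 29 comes from multiplying up: 24 × (1 + 0.20) = 28.8, rounded up to 29. To have n completers after a proportion d is lost, one recruits n / (1 − d): 24 / 0.80 = 30, or 15 per arm. Check: 29 × 0.80 = 23.2, just under 24; 30 × 0.80 = 24. The slip is one participant. (This 29 in total is not the 29 per arm in the next paragraph of Sample Size, which comes from a separate ANCOVA calculation.)

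**Main target.**

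- If 40 is the number recruited: 40 × 0.80 = 32 completers, 16 per arm.
- If 40 is the number completing: 40 / 0.80 = 50 recruited, 25 per arm.
- If exactly 20 are recruited in an arm and each completes with probability 0.80, the chance that all 20 complete is 0.80^20 = 0.0115, about 1%.

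Other dropout rates, as assumptions around the stated 20%:

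| Dropout | Completers per arm if 40 recruited | Recruits needed for 40 completers |
|---|---|---|
| 10% | 18 | 45 |
| 20% | 16 | 50 |
| 30% | 14 | 58 |

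**Does the recruitment rate settle it?** 5 × 6 = 30 and 10 × 6 = 60. Recruiting 40 takes 40 / 6 = 6.7 a month and recruiting 50 takes 50 / 6 = 8.3 a month. Both lie inside the stated range. Its lower end, 30, falls short of 40 completers even with no dropout. The rate therefore does not show which target is meant.

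**Effect on precision.** The standard error of a difference in means is proportional to √(2/n), with n per arm. Going from 20 to 16 multiplies it by √(20/16) = 1.118, an increase of about 12%. This needs no assumption about the outcome SD.

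**Illustration in CDS points, resting on assumptions.** The protocol does not print an SD. An SD of about 69 is inferred here from its change of 36 points and effect size of 0.52 (36 / 0.52 = 69.2). The ANCOVA 95% half-width is t × SD × √(1 − r²) × √(2/n), with t on 37 degrees of freedom (2.026) for 20 per arm and 29 (2.045) for 16 per arm.

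- r = 0.9 (stated): 2.026 × 69.2 × 0.436 × 0.316 = 19.3 with 20 per arm; 2.045 × 69.2 × 0.436 × 0.354 = 21.8 with 16.
- r = 0.7 (assumed, not in the protocol): about 32 with 20 per arm and about 36 with 16.

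The half-width grows by about 13%, slightly more than the standard error because the t quantile also rises.

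**The case against.** The strongest reply is that this is a feasibility study which states that it has no formal sample size calculation, calls its dropout rate nominal, and would still exceed the cited minimum of 12 per arm with 16. A precision loss of about 12% is modest where no confirmatory test is planned. All of that stands, and it is why the point is moderate. It does not remove the conflict between the two definitions.

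Three stronger readings are tempting, and the document does not support them.

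- *The design delivers 16 per arm, not 20.* This holds only if 40 is the number recruited. Under the completer wording, 50 recruits fit within the stated monthly rate and would be expected to give 20 per arm.
- *The wrong dropout inflation causes the shortfall.* The 29 belongs to the 24-participant minimum and is never applied to the 40. Changing it to 30 leaves the main target as it was. The 16 arises because the 40 carries no dropout allowance.
- *The same result would be a success in one section and a failure in another.* The protocol sets no numerical pass mark for recruitment or retention. One can say only that a stated aim is met or missed.

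Nor is there a printed interval width that has been shown to be wrong. The statement on precision is qualitative.

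**Conclusion.** The inconsistency is real and can be checked from the protocol alone. Twenty per arm is the number recruited in three places and the number completing in two, and at the protocol's own dropout rate these differ by 8 completers (40 against 32) or by 10 recruits (50 against 40). The sentence on magnitude, direction and precision is tied to "Our planned recruitment of 20 per arm", so for that sentence the expected analysable number at 20% dropout is 16 per arm. These sizes rest on the nominal 20% applying equally to both arms; the CDS half-widths rest in addition on an inferred SD and, for r = 0.7, on an assumed correlation. The minimum of 29 is a separate slip of one participant. Severity: moderate.

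**What to change.** State one target, in the same words, in the Abstract, Participants and Sample Size.

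- **Low-cost version:** keep 40 recruited (20 per arm), say that about 32 (16 per arm) are expected to complete at 20% dropout, reword the two completer sentences to match, and tie the precision statement to 16 per arm. This costs wording only, plus a slightly less favourable precision statement.
- **If 40 completers is the real aim:** give 50 (25 per arm) as the recruitment number in all three sections. This costs 10 further participants, at 8.3 a month within the stated range.

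In either case, change the inflated pilot minimum from 29 to 30. If interval widths in CDS points are added, state the SD and correlation behind them and label as assumptions any that the cited data do not supply.

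### The required 29 participants per arm by ANCOVA is not reproduced from the effect size and correlation given for it, and is not reconciled with the 20 per arm called sufficient

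*Protocol*

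**What the plan says.** The Sample Size section opens: "There is no formal sample size calculation, or priori power calculation". It bases the minimum on a pilot-study rule of 12 per arm (24 in total, 29 after a nominal 20% dropout) and sets a target of 20 completers per arm.

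Its second paragraph turns to an earlier self-controlled cross-over study, which "found the effect size between the treatment period and the waiting period to be 0.52". It adds: "This translated into a decrease of 36 points on the CDS Scale". From that difference, a correlation of 0.9 and the CDS standard deviation in each phase (not printed), it says "we anticipated that the required sample size would be 29 participants per arm (using the ANCOVA method".

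The next sentence reads: "Our planned recruitment of 20 per arm provides sufficient power to provide information on the magnitude, direction, and precision of the treatment effect", the purpose being to help power a later definitive trial.

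The Background gives a result for 36 participants from the same clinic, citing the same study: "A mean decrease in trait DDD symptoms (Mean = -33.67; [95% C.I: -45.14 to -22.20]) was observed".

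**The concern.** A correlation of 0.9 removes 81% of the outcome variance in an ANCOVA. A standardised effect of 0.52 should then need far fewer than 29 per arm, so the stated requirement looks too large for its own inputs.

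Three statements in the section also do not fit together: there is no power calculation, 29 per arm are required, and 20 per arm provide sufficient power. If 29 per arm were a correct requirement for 80% power, 20 per arm would fall short of it. If the printed inputs are correct, 20 per arm exceed what is needed. A reader cannot tell which holds, and so cannot judge how informative the estimated effect on the CDS will be.

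**Working it through.** **Inputs from the documents.** Effect size d = 0.52, difference 36 CDS points, correlation r = 0.9, ANCOVA, stated n = 29 per arm, planned n = 20 per arm (all Sample Size). Mean change -33.67, 95% CI -45.14 to -22.20, 36 participants (Background). CDS range 0 to 290 (Table 2).

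**Assumptions, because the protocol prints no value.** Two-sided alpha 0.05; power 80% or 90%; SD = 36/0.52 = 69.2, unless stated otherwise.

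**1. Attempt to reproduce 29 per arm.** For ANCOVA, n per arm = 2(z_alpha + z_power)² (1 - r²)/d², with 1 - r² = 0.19 and d² = 0.2704.
- 80% power: 2 × 7.849 × 0.19/0.2704 = 11.03, so 12; 13 with the noncentral t on 2n - 3 degrees of freedom.
- 90% power: 2 × 10.507 × 0.19/0.2704 = 14.77, so 15; 16 with the t correction.

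The stated 29 is not reproduced.

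**2. Does the SD implied by the Background explain it?** This step assumes that the interval is for a within-person change in 36 participants.
- Half-width: (45.14 - 22.20)/2 = 11.47.
- SD of change: 11.47 × 6/2.030 = 33.9 using t, or 11.47 × 6/1.96 = 35.1 using z.
- With r = 0.9, CDS SD = SD of change/√(2(1 - 0.9)), which is 75.8 or 78.5.
- For 36 points, d is then 0.475 or 0.459.

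| CDS SD | 80% power (with t) | 90% power (with t) |
|---|---|---|
| 69.2 | 11.0 (13) | 14.8 (16) |
| 75.8 | 13.2 (15) | 17.7 (19) |
| 78.5 | 14.2 (16) | 19.0 (21) |

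The implied SD widens the range to about 13 to 21 per arm, still below 29.

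**3. Other settings on the printed inputs (SD 69.2).** The first five lines are per arm, at 80% then 90% power where two figures are given.
- Change-score analysis, factor 2(1 - r): 11.6 and 15.5.
- Follow-up score only, with no baseline adjustment: 58.1 and 77.7.
- ANCOVA at alpha 0.01: 16.4 and 20.9.
- ANCOVA at 5% with 95% or 99% power: 18.3 or 25.8.
- ANCOVA with 20% dropout (12/0.8 and 15/0.8): 15 and 19.
- If 0.52 were 36 divided by the SD of change, r = 0.9 would need a CDS SD of 69.2/√0.2 = 155. A 0 to 290 scale allows at most about 145.

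**4. What would give 29 by ANCOVA, before any dropout allowance.**
- Keeping d = 0.52: r = 0.71 at 80% power or 0.79 at 90%.
- Keeping r = 0.9 and 36 points: an SD of 112 at 80% power or 97 at 90%, against the 69 implied.

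**5. What the discrepancy means for 20 per arm.**
- On the printed inputs (SD 69.2), power is about 96%.
- If 29 per arm were the correct requirement, power at 20 is Φ(√(20/29)(1.96 + z_power) - 1.96): 64% if 29 was set for 80% power, 77% if for 90%.

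**6. Precision at 20 completers per arm.** The 95% CI half-width of the baseline-adjusted difference is t × SD × √((1 - r²) × 2/20), with t = 2.026 (37 df) and SD 69.2:
- r = 0.9: 19 points.
- r = 0.7: 32 points.
- r = 0.5: 38 points.

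**The case against.** The strongest reply is that the calculation is undocumented rather than wrong. It used phase-specific SDs that are not printed, and alpha, power and the definition of the effect size are not given either. Small departures can reach 29. With r = 0.85 (which rounds to 0.9), SD 69.2, 90% power and the t correction, ANCOVA gives 23 per arm, and 23/0.8 = 28.75. The Background's 33.67 points with SD 78.5 and r = 0.9 also gives 23 at 90% power.

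Part of this stands: 29 cannot be called impossible, and 11 to 16 rests on assumptions. But the first route replaces the stated correlation and the second the stated difference. Both also divide by 0.8, whereas the section's own allowance multiplies by 1.2 (24 × 1.2 = 28.8, giving 29). By that convention 23 becomes 27.6, or 28.

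The second reply is that the sentence about sufficient power concerns information on magnitude, direction and precision, not a test of efficacy. That is fair and lowers the seriousness. It does not explain why 29 per arm are called required in the sentence before.

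A reader might also infer the following, which the document does not support:
- **That a paired formula was used.** (1.96 + 0.842)²/0.52² = 29.03 matches. So does the two-arm ANCOVA total at 90% power (2 × 14.77 = 29.5), and 29 is also the section's recruitment total for the 24-participant minimum. The document cannot show which, if any, is the source.
- **That the definitive trial will inherit the error.** Aim 2 and the Analyses section size that trial from this study's own pooled SD and baseline-to-follow-up correlation, with the clinically important difference.
- **That Aim 3 is only a significance check.** It does plan to "check if a signal has been detected in the treatment arm versus the control arm", but it also lists the size, direction and uncertainty of the effect. The abstract's "the probability that the results have been obtained by chance" is a separate matter of wording.

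**Conclusion.** The point holds as a stated figure that is not reproduced from its stated inputs. Under a two-sided 5% test, the effect size, difference and correlation give about 11 to 13 per arm at 80% power and 15 to 16 at 90% with SD 69, or about 13 to 21 across both powers with SD 76 to 79, against the printed 29. The section also leaves three statements unreconciled: no formal calculation, 29 per arm required, and 20 per arm sufficient.

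It would be tempting to conclude that the trial is too small. The document does not support that: the 40 participants rest on a pilot rule of thumb and on feasibility, and on the printed inputs 20 per arm would be more than enough. Nothing in recruitment or conduct depends on the 29. Severity is moderate: a printed figure needs correcting, and the trial's conduct is not threatened.

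**What to change.** In the Sample Size section:

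1. Recompute the figure from the actual phase SDs and replace 29 per arm with the result, stating alpha, sidedness, power, SDs, correlation, formula and any dropout allowance. Otherwise remove the figure. Do not write in 13 or 16 without those SDs, because both rest on an inferred SD.
2. Align the opening denial of a formal calculation with whatever is kept, for example by saying that the calculation is illustrative and did not set the target of 40.
3. Replace the claim of sufficient power with the expected 95% CI half-width for the baseline-adjusted CDS difference at 20 completers per arm: about 19, 32 and 38 points for r = 0.9, 0.7 and 0.5, assuming SD 69, updated once the actual SDs are stated.

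The cost is the rewording of one section. No participants, visits or analyses are added.

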### Analyses

We will seek evidence of the feasibility of conducting a larger subsequent RCT by examining the following parameters:

- Power calculation: We will determine the pooled standard deviation for the baseline score of the primary outcome variable, as well as the correlation of the primary outcome at baseline and at follow-up (T3). These data, along with the mean clinically important difference (MCID), will be used in the sample size calculation for a fully powered subsequent study.
- Recruitment: Number of referrals from each source, numbers ineligible, reasons for ineligibility, rates, and reasons for refusal to be included in the study.
- Randomisation: whether groups are balanced and randomisation possible in this environment.
- Withdrawals: Attrition rates and reasons for withdrawing throughout the study, follow-up rates.

Additionally, to fulfil the secondary objectives, descriptive analyses will be performed on the following outcomes: resources needed to complete CBT-f-DDD; health economics evaluation; therapist adherence to CBT-f-DDD; sample characteristics; and acceptability outcomes.

Qualitative data from interviews with therapists and participants will be transcribed and analysed using thematic analysis within NVivo software (supervised by co-applicant [name]). This will be guided by Braun & Clarke’s six stage process (42), and conducted collaboratively to include the perspectives of clinicians and those with lived experience within the research team. Interviews will be recorded using an encrypted device for the audio recording, and data will be stored securely within the NHS. Transcription of this audio recording will be done by a professional external agency which has an over-arching contract with UCL that covers all GDPR issues (as outlined in the collaboration agreement between UCL and C&I). These audio files will be destroyed at the end of the project.

As well as providing an in-depth exploration of treatment experiences and perceived impacts (from both provider and recipient perspectives), analysis will be structured to produce clear summaries of feasibility and acceptability issues as reported by therapists and participants. These analyses will inform therapy and trial process modifications in advance of any subsequent definitive trial.

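### The Sample Size section offers this trial's own treatment effect as a basis for powering the definitive RCT; Analyses and Aim 2 do not use it, and 20 per arm is too few for it

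*Protocol*

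**What the plan says.** Three places in the protocol bear on how the definitive RCT will be sized.

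- **Sample Size** defends 20 per arm on the ground that it gives "information on the magnitude, direction, and precision of the treatment effect from the feasibility study to power (with sufficient precision) a subsequent definitive RCT".
- **Analyses**, in the item on the power calculation, names the pooled baseline SD of the primary outcome and its baseline-to-T3 correlation, then adds: "These data, along with the mean clinically important difference (MCID), will be used in the sample size calculation for a fully powered subsequent study". The observed effect is not an input.
- **Aims and Objectives** agrees with Analyses. Aim 2 is to "Define the parameters to inform the sample size calculation for a future efficacy trial (RCT"), and lists the CDS correlation and pooled baseline SD. Aim 3 treats the efficacy estimate separately, as a check for a signal, "so as to inform a subsequent larger RCT if appropriate".

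The protocol gives no value for the MCID.

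**The concern.** The target difference is the most influential input to a sample size, because the number needed varies with the inverse square of it. Analyses takes it from an MCID, which does not depend on what this trial observes. Sample Size points to the effect estimated here. Just before that, the same section sizes a trial on an observed effect from an earlier study, which makes the second reading the natural one.

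Supplying inputs for the definitive calculation is a main purpose of this trial. If its effect estimate were used as the target, chance would largely decide the size of the next trial, and the claim of sufficient precision would lend that a support it does not have.

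**Working it through.** **Inputs.** From Sample Size: the earlier study "found the effect size between the treatment period and the waiting period to be 0.52"; "This translated into a decrease of 36 points on the CDS Scale"; and "a correlation of 0.9 which was observed for intra-participant correlation". That section also relies on "the standard deviation of the CDS at each phase of the crossover study", but prints no SD. I derive SD = 36/0.52 = 69.2. Assumed here: two-sided 5% level, 90% power for the definitive RCT, and r = 0.7 as a less favourable alternative. SD and r are treated as known.

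**1. The protocol's own figure.** ANCOVA: n per arm = 2 × (z₁ + z₂)² / d² × (1 − r²), with 1 − 0.9² = 0.19.

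- 80% power: 2 × (1.960 + 0.842)² / 0.52² = 58.1; × 0.19 = 11.0, so 12 per arm.
- 90% power: 2 × (1.960 + 1.282)² / 0.52² = 77.7; × 0.19 = 14.8, so 15 per arm.

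The stated 29 per arm is not reproduced. At 80% power it would need r of about 0.71, or an SD of about 112. The results below are therefore conditional on the derived SD.

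**2. Precision with 20 per arm.** Residual SD = 69.2 × √(1 − r²); SE = residual SD × √(2/20); half-width = 1.96 × SE.

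- r = 0.9: residual SD 30.2, SE 9.5, half-width 18.7 points. Around 36 the interval is 17.3 to 54.7.
- r = 0.7: residual SD 49.4, SE 15.6, half-width 30.6 points.

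Even at r = 0.9, the sample sizes implied by the two limits differ by (54.7/17.3)² = 10-fold.

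**3. Sizing the RCT on the estimate (r = 0.9, true effect 36).** n per arm = 2 × (30.2 × 3.24 / estimate)². On the true effect this is 15. The 10th and 90th percentiles of the estimate are 36 ± 1.28 × 9.54, or 23.8 and 48.2, which give n of 33.9 and 8.2.

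True power = Φ(3.24 × 36 / estimate − 1.96). It is below 80% when the estimate exceeds 36 × 3.24 / 2.80 = 41.7, which is (41.7 − 36)/9.54 = 0.59 SE above the truth: probability 28%. In simulation, with n rounded up, it is 27%.

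**4. Sensitivity** (simulation, n rounded up for the power columns; only positive estimates carried forward).

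| True effect | r | RCT proceeds if | n per arm on true effect | 10th–90th percentile of n | True power < 80% | Mean power |
|---|---|---|---|---|---|---|
| 36 | 0.9 | estimate positive | 15 | about 8–34 | 27% | 0.88 |
| 36 | 0.9 | estimate/SE > 1.96 | 15 | not tabulated | not tabulated | 0.87 |
| 24 | 0.9 | estimate/SE > 1.96 | 34 | not tabulated | 46% | 0.78 |
| 36 | 0.7 | estimate positive | 40 | about 16–182 | 35% | 0.84 |
| 36 | 0.7 | estimate/SE > 1.96 | 40 | not tabulated | 55% | 0.75 |

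The true effect of 24, r = 0.7 and the significance condition are assumptions, not figures from the protocol.

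**The case against.** The strongest reply is that Sample Size only justifies the size of this trial. It names no target difference and no formula for the next one. The two places that set out the inputs, Analyses and Aim 2, leave the observed effect out, and an effect with its interval can properly inform a later trial as a plausibility check. This stands in part. A reader might infer that the protocol commits itself to the observed point estimate as the target difference, and the text does not say that. What remains is an unreconciled sentence whose natural meaning conflicts with Analyses, and a claim of precision that its own figures do not bear out.

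A reader might also infer that the definitive RCT would often be underpowered, or systematically too small. The documents do not support that. On the protocol's effect and correlation, mean power is 0.88 against a planned 0.90, and 0.87 even if only significant results lead on. An unselected estimate errs upward as often as downward, so oversizing is as likely as undersizing. The heavier losses need a smaller effect, a lower correlation or a selective decision to proceed. Aim 3 looks for a signal but sets no significance threshold and no go/no-go rule.

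Finally, the definitive RCT would need its own sample-size justification, and nothing here alters the conduct, data or analysis of the present trial. That is a fair reason to rate the point low.

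**Conclusion.** The inconsistency holds as a matter of text and needs no calculation: Sample Size brings in the observed effect, while Analyses and Aim 2 do not. The arithmetic adds that 20 per arm gives an effect estimate good to about ±19 CDS points at r = 0.9 and ±31 at r = 0.7. That is not sufficient precision for choosing a target difference when the effect in question is 36.

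The size of the consequence rests on the derived SD, the assumed significance level and power, and r and SD being treated as known. No MCID-based sample size can be set beside these figures, because no MCID value is given. Minor severity: the sound rule is already in the protocol, and one passage needs to be brought into line with it.

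**What to change.** In Sample Size, replace the clause on powering the definitive RCT, and drop its bracketed claim of sufficient precision. Suggested wording: *This trial will supply the baseline SD and the baseline-to-follow-up correlation of the CDS for the definitive sample size calculation. The target difference of that calculation will be the MCID (see Analyses). The estimated treatment effect and its confidence interval will be reported only as a check on whether the MCID is plausible.*

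Align the bracketed text in Aim 3 so that informing a larger RCT means this plausibility check. Choosing the MCID before unblinding is desirable but not essential to the correction.

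The cost is a wording change in two sections, with no extra participants, data or analysis.
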